## Materials and methods

2

### Study design

2.1

A three-arm, single-blind randomized controlled trial with repeated assessments at baseline, post-intervention, and two-week follow-up. EMA surveys will also be administered throughout the intervention period. Eligible participants will be randomly assigned to one of three study conditions in a 1:1:1 ratio: (1) Reading What Matters (RWM), in which participants will complete the values-based microinterventions in a standard written format; (2) Capturing What Matters (CWM), in which participants will complete the values-based microinterventions with the visual support of photography; and (3) control condition, in which participants will not complete any of the microinterventions and will only receive daily notifications to complete the assessment protocol. Fig. 1 shows the study design.

**Fig. 1 fig1:**
[figure not shown]
Study design.

This study will be conducted entirely online, and the microinterventions will be delivered via a study mobile phone application. Participants in all study conditions will be required to download and use the application on their personal smartphones.

### Sample size calculation

2.2

Currently, few studies have examined the effects of mobile phone-based microinterventions targeting valued living. To date, web interventions targeting valued living have reported effect sizes of *d* = 0.27 for hedonic well-being compared to no treatment [15]. Similarly, Bojanowska et al. [14] found *η*^2^ = 0.09 for hedonic well-being and *η*^2^ = 0.08 for eudaimonic well-being compared to a non-active control group. Therefore, the sample size for this study is determined based on effect sizes observed in prior studies (*f*^*2*^ ranging from 0.19 to 0.31). Specifically, we conducted a power analysis to detect an effect size of *f*^*2*^ = 0.25 for the within-between interaction in a repeated measures ANOVA with three groups (RWM, CWM, control) and three measurement points (baseline, post-intervention/two-week follow-up), with a significance level of 0.05 and statistical power of 0.80. The required sample size for the main analysis was 159 participants in total.

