The proposed study also presents some limitations that should be considered. First, the English-language requirement may introduce selection bias and limit the generalisability of the findings, as students with lower English proficiency may be less likely to participate. Making the study materials available in both English and Dutch may broaden accessibility and enable future cross-cultural investigations. Moreover, participants may differ in motivation, expectations, or engagement depending on the pathway through which they enter the study, particularly when participation is linked to course credit. Although participants will be randomized and recruitment pathways will be recorded and examined across study arms, residual differences related to recruitment context may still influence adherence or outcome responses. Attrition is also expected in longitudinal experimental designs, especially in mobile phone-based interventions [[71], [72], [73]]. Difficulties in completing the tasks assigned during the intervention or a lack of understanding of the intervention rationale may increase this risk. To minimize the likelihood of drop-out, a predefined schedule with the study notifications will be sent to participants before the intervention period begins. A further limitation concerns the use of study-specific EMA items. Although these items were designed to assess theoretically relevant momentary constructs, their reliability and validity is yet to be established, and results involving these measures should be interpreted cautiously. Additionally, research has shown that internet-based interventions may have negative effects in some cases [74], including the worsening of existing symptoms or the emergence of new symptoms not directly addressed by the intervention. Values are also a sensitive topic and may evoke a range of emotional reactions. To provide support, a contact number and email address will be available throughout the study, particularly at the beginning of the intervention. This support will be available for both technical difficulties related to the app and emotional issues arising from the intervention. From the start of the study until the follow-up assessment, participants will be able to contact the research team by phone, text message, or email if they experience any of these difficulties. Previous research has shown that support in internet-based interventions is positively associated with treatment outcomes [75].

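### Section 2.2 labels Cohen's f as f², takes too large a lower effect from d = 0.27, and states an N of 159 that its named 3×3 interaction does not give

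*Protocol article*

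**What the plan says.** Section 2.2 (Sample size calculation) cites two sources of prior effects. One is a standardised difference of "0.27 for hedonic well-being compared to no treatment". The other is a study with η² = 0.09 (hedonic) and 0.08 (eudaimonic well-being) against a non-active control. The section summarises these as f² values "ranging from 0.19 to 0.31".

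The planning effect is an f² of 0.25, at α = 0.05 and 80% power. The calculation is said to be "for the within-between interaction in a repeated measures ANOVA with three groups (RWM, CWM, control) and three measurement points". A parenthesis then lists the time points and joins the last two with a slash. The resulting number is given as follows: "The required sample size for the main analysis was 159 participants in total". No correlation among repeated measures (ρ), sphericity correction (ε) or effect-size convention is given.

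Section 2.11 (Statistical analysis) plans the matching test for the distal outcomes: a mixed ANOVA with three conditions and three time points, so the interaction has 4 numerator degrees of freedom.

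**The concern.** Three statements in section 2.2 do not fit together.

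- The effect-size symbol does not agree with the η² values cited beside it.
- The lower end of the range does not agree with the d cited beside it.
- The sample size does not agree with the test and effect size named.

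The section presents 159 as derived from previously observed effects at 80% power. A reader of the results will use that claim to judge what a null finding means. If the range of prior effects is wrong at the lower end, and the test behind 159 is not the one described, the claim cannot be used that way.

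**Working it through.** **Inputs from the article.** d = 0.27; η² = 0.09 and 0.08; stated range 0.19 to 0.31; planning value 0.25; k = 3 groups, allocated 1:1:1; m = 3 time points; α = 0.05; power 0.80; N = 159. **Not stated, so assumed over a range:** ρ from 0 to 0.8; ε of 1, 0.75 or 0.5; the noncentrality convention.

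**Step 1: the label.** f² = η²/(1 − η²).

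- η² = 0.09: f² = 0.09/0.91 = 0.099, f = 0.314.
- η² = 0.08: f² = 0.08/0.92 = 0.087, f = 0.295.

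The stated upper end, 0.31, is therefore f. A literal f² = 0.25 means f = 0.50 and η² = 0.25/1.25 = 0.20, more than twice the cited values.

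**Step 2: the lower end.** For two equal groups f = d/2 = 0.27/2 = 0.135, and f² = 0.018. The stated 0.19 is neither. It matches 0.27/√2 = 0.191, but the article does not show how it was obtained.

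**Step 3: a calculation that returns 159.** A three-group F test with 2 and N − 3 degrees of freedom, with λ = N·f² and f = 0.25:

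- N = 156: power 0.797.
- N = 159: λ = 159 × 0.0625 = 9.94, power 0.805.

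So 159 is the first multiple of three to reach 0.80.

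**Step 4: the test named.** For the interaction, df1 = (k − 1)(m − 1)ε and df2 = (N − k)(m − 1)ε. Three conventions for λ are in use:

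- (a) λ = N·m·f²·ε/(1 − ρ)
- (b) λ = N·(m − 1)·f²·ε
- (c) λ = (N − k)·(m − 1)·f²·ε

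Smallest total N, as a multiple of three, with power of at least 0.80:

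| 3×3 interaction | (a), ρ = 0 | (a), ρ = 0.5 | (a), ρ = 0.7 | (b) | (c) |
|---|---|---|---|---|---|
| f² = 0.25 literally, ε = 1 | 21 | 12 | 9 | 27 | 30 |
| f² = 0.25 literally, ε = 0.5 | 30 | 18 | 12 | 42 | 45 |
| f = 0.25, ε = 1 | 69 | 36 | 24 | 99 | 102 |
| f = 0.25, ε = 0.75 | 81 | 42 | 27 | 120 | 123 |
| f = 0.25, ε = 0.5 | 108 | 57 | 36 | 159 | 162 |

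At a literal f² = 0.25 nothing comes near 159. At f = 0.25 the 3×3 interaction returns 159 only under convention (b) with ε = 0.5. That setting reduces df1 to 4 × 0.5 = 2 and λ to N·f², which is the test of Step 3. A 3×2 interaction under (b) is also the same calculation.

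**Step 5: power at N = 159 over the effect range.**

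| f | 2-df test | 3×3, ε = 1, convention (c) | 3×3, ε = 1, convention (a), ρ = 0.5 |
|---|---|---|---|
| 0.25 | 0.80 | 0.96 | > 0.99 |
| 0.19 (stated lower end) | 0.56 | 0.77 | > 0.99 |
| 0.135 (converted from d = 0.27) | 0.31 | 0.44 | 0.93 |

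**The case against.** The strongest reply is that the design named may be the one that was run. A 3×3 interaction at f = 0.25 with ε = 0.5 does return 159. The slash between the post-intervention and follow-up assessments in section 2.2 might also mean baseline against one later point, and a 3×2 interaction can give 159 too. A condensed article may leave ρ and ε to the full protocol. This stands against any claim to know which calculation was run. A reader might infer from the exact match in Step 3 that a one-way ANOVA was used; the document does not support that. The reply does not rescue the text as printed. Each of these routes needs f = 0.25 rather than f² = 0.25, and each needs either an unstated ε of 0.5 or a number of time points that conflicts with section 2.11.

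A reader might also infer that the trial is too small for its planned test. That does not follow. At f = 0.25 with ε = 1, power for the 3×3 interaction is about 0.96 or more at 159. Under the least favourable of the three conventions it is still about 0.84 if 30% of participants (an assumed rate) were incomplete.

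Two further inferences go beyond the document:

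- **Attrition.** The Discussion says "Attrition is also expected in longitudinal experimental designs, especially in mobile phone-based interventions", and section 2.2 mentions no allowance. But 159 is described as the number for the main analysis and not as the recruitment target, and an allowance may sit in the full protocol.
- **Hypothesis 2.** A detectable difference between the two active arms would be a useful addition, but its absence is not a wrong statement.

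The 0.27/√2 explanation for 0.19 fits numerically but remains a conjecture.

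**Conclusion.** The power basis in section 2.2 is wrong as written in three respects.

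1. The values labelled f² are on the f scale. This follows from the article's own η² values and needs no assumption.
2. The lower end of the prior-effect range should be 0.135, not 0.19, if d = 0.27 compares two groups of equal size.
3. The stated test and effect size do not give 159. This holds for a literal f² = 0.25 under every setting tried, and for f = 0.25 unless an unstated ε of 0.5 and a partial-effect convention are both assumed.

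At the planning value f = 0.25 the mismatch works in the trial's favour. The cost appears at the smallest cited effect: power at f = 0.135 is about 0.31 if the 2-df calculation is the relevant one, and 0.44 to 0.93 for the 3×3 interaction with ε = 1 (the top value at ρ = 0.5). The article therefore cannot claim 80% power across the effects it cites without stating its convention, ρ and ε. This is an error in the stated justification; it does not affect any planned estimate or test.

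**What to change.** Rewrite section 2.2 as follows.

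- Label the effect size Cohen's f, and give the cited effects as f = 0.135, 0.295 and 0.314 (range 0.135 to 0.31).
- State the calculation that yields 159: the test, number of time points, effect-size convention, ρ and ε. Otherwise, recompute for the 3×3 interaction planned in section 2.11 with those settings given.
- Remove the ambiguity of the slash in the list of measurement points.
- Restate the power at N = 159 over the corrected range, including f = 0.135.

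The cost is the text of one section and about an hour of calculation. No design change and no extra participants are needed.

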### Study population

2.3

Recruitment will be conducted at universities in the Netherlands, targeting students pursuing bachelor's, master's, and PhD degrees. Participants will be eligible for inclusion if they are (a) at least 18 years old, (b) have access to a mobile phone and the internet, (c) enrolled as students at a university in the Netherlands, and (d) able to understand and write in English. English will be used as the sole study language to ensure that the same intervention instructions, EMA items, and self-report measures are delivered across participants and conditions. Introducing Dutch or other versions would require formal translation, cultural adaptation, and additional validation to ensure psychometric and conceptual equivalence. It could also introduce subgroup effects that would require additional analyses beyond the scope of the current study.

Exclusion criteria will include (a) being over 45 years old, (b) currently having a diagnosis of a severe mental disorder, such as bipolar disorder, schizophrenia, or borderline personality disorder, (c) taking psychiatric medication, (d) currently receiving psychological or psychiatric treatment for a specific mental disorder, or (e) reporting any suicidal ideation (i.e., scoring above 0 on item 9 of the Patient Health Questionnaire; [49]). Individuals who do not meet the inclusion criteria will be offered alternative resources, such as links to psychological services or opportunities to participate in other lab studies.

### Recruitment

2.4

The study will be advertised online via LinkedIn, Instagram, and Facebook. In addition, advertisements, including posters and flyers, will be distributed across university campuses. These materials will include a QR code directing interested individuals to the initial study survey and informed consent form. Individuals interested in participating will be required to provide informed consent and complete an initial questionnaire to determine their eligibility based on the inclusion criteria. Additionally, the SONA system, used by the BMS Faculty at the University of Twente, will be used to assign credits to psychology and communication students for their participation.

To account for potential differences associated with recruitment pathways, the source through which participants enter the study will be recorded. Because randomization will occur after enrollment, recruitment sources are expected to be distributed across study conditions. Nevertheless, their distribution will be examined descriptively across study arms to identify any potential imbalance. If meaningful imbalances are observed, sensitivity analyses will be conducted to examine whether recruitment source affects the main findings.

### Values-based microinterventions

2.5

We developed three values-based microinterventions for this study: 50th birthday party, 3-min wake-up, and friendly reminder. Each microintervention is described in detail below.

#### Standard microinterventions

2.5.1

Participants assigned to the RWM condition will receive the standard version of the values-based microinterventions described below.

The 50th birthday party aims for helping participants to clarify their central personal values. This microintervention is a 10-min guided visualization in which participants imagine celebrating their 50th birthday surrounded by people they would like to attend. This exercise is a modification of the original ACT strategy *Attending Your Own Funeral* [45]. In the original exercise, individuals are asked to imagine their own funeral, the people that they would love to be surrounded with, and choose three individuals to envision what they might say about them and the life they have lived. In our adapted version, participants will be asked to imagine their 50th birthday party, as this scenario is more accessible and relatable for university students who may find imagining their funeral too distant or complex. This modification also avoids the sensitive topic of death, which could evoke distressing emotions and may be risky in a self-guided intervention without professional support. As in the original exercise, participants select three people and focus on what they would *like* these people to say about them and the life they had lived, rather than what they might probably say. To guide the visualization, participants are prompted with the questions: “What does this person say about how you have lived your life? What does this person say about how you have dedicated your time and energy in recent years? What does this person say about what you have valued as important in your life?” After completing the visualization, participants reflect and write about their experience, answering the following open question: “What words did these people use to describe the person you have become and the life you have chosen to live?” Then, participants will be asked to identify their core values by answering the following question: “After the audio: What things in this world are most important to you above all else?” They will then create a ranked list of 5 core personal values, ordered from most to least important. To help participants articulate meaningful values while avoiding vague or overly simplistic terms, examples will be provided reflecting values as ways of being, acting, or living important for the individual. These examples might include: “For me, taking loving care of my dog is meaningful, or being an ambitious person is something really important for me …” The values written will be stored by the app and will be displayed to them in the following microinterventions.

The 3-min wake-up aims to increase awareness of personal values, identify valued actions, and encourage engagement with them. This microintervention consists of a daily 3-min guided visualization exercise. Before the audio, participants will read their values displayed on the screen, and will be asked to notice what these values evoke in them at that moment. After this, participants will engage with the audio. Firstly, they are encouraged to connect with each value and reflect on why these values are important and meaningful to them. Second, participants are guided to visualize moments during the day in which they could act in line with their values, encouraging them to engage in valued actions and carry this sense of alignment throughout the day.

The friendly reminder encourages participants to become more aware of their personal values throughout the day. This microintervention consists of a text notification. In this strategy, participants will receive a text message prompting them to read and become aware of their personal values. Participants will receive the following message: “Now, take a moment and read your central values”, and their values will be displayed on screen.

#### Microinterventions with photography

2.5.2

Participants assigned to the CWM condition will receive the same three types of microinterventions as those in the RWM condition, with the addition of a photography component.

The 50th birthday party microintervention will be delivered in the same way as the previous condition. However, after listening to the audio and writing about the experience, participants will be asked to take 5 photos (or select them from their gallery), each representing one of the 5 values they wrote earlier. Then, they will create a folder in their photos app to store these photos, naming the folder as they wish for future use.

The 3-min wake-up will follow the same structure for both groups. However, before the audio, participants will be redirected to the folder where they saved their photos of values. Participants will be asked to notice what these photos evoke in them at that moment. Upon returning to the app, there will be a control question asking if they have looked at the photos.

For the friendly reminder, participants will receive the message: “Now, take a moment, go to your values folder, and look at the photos of your central values”.

### Control group

2.6

Participants in the control group will not receive any of the microinterventions and will only be assessed daily with the EMA pre-questions, in addition to the assessments at time points 1 (baseline), 2 (post), and 3 (follow-up). After the follow-up, participants in the control condition will receive an email offering them the opportunity to randomly receive one of the two interventions.

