### Procedure

2.8

Interested participants will access it through a link or QR code provided in the advertisements. The study will comprise 4 steps. In Step 1, students will begin by completing an initial web-based survey on Qualtrics. This survey will provide detailed information about the study and include the informed consent form. To minimize response bias, the specific research questions and hypotheses will not be disclosed during participation. The survey will also collect sociodemographic and clinical data, as well as responses to baseline validated questionnaires. Sociodemographic data will include age, gender identity, marital status, education level, nationality, and university enrollment. Clinical data will include information on whether participants are currently receiving psychiatric or psychological treatment for a specific mental disorder and whether they have been professionally diagnosed with a severe mental disorder. Participants who do not meet the eligibility criteria will be excluded due to the emotional sensitivity that the interventions might elicit and the absence of therapist guidance, which could increase the risk of iatrogenic effects. These participants will receive an email thanking them for their interest and informing them that they are not eligible for participation.

Additionally, participants who select any option other than “not at all” on item 9 of the PHQ will receive an email containing links to psychological resources for accessing mental health support. These resources will include https://findahelpline.com/countries/nl and https://www.government.nl/topics/mental-health-services/question-and-answer/help-for-mental-health-problems. These participants will also be excluded from the study.

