**Fig. 3 fig3:**
[figure not shown]
Design of the TIIM mobile-based app intervention.

Once participants register in the TIIM app and enroll in the study, they will be randomly assigned in a 1:1:1 ratio to one of three groups: RWM, CWM, or the control group. Randomization will be performed using the Study Randomizer software [50]. After enrollment, participants will receive a schedule outlining the microinterventions to be completed during the study. Reminder emails will be sent to encourage participants to download the app and complete enrollment.

In Step 2, participants will begin receiving daily notifications throughout the 7-day intervention period. These notifications will include the scheduled microinterventions and brief EMA questions administered before and after each exercise.

In Step 3, participants will complete the post-intervention assessment one day after the 7-day intervention period. This assessment will be administered through the TIIM app via a notification that will remain available for 24 h. When participants do not complete the post-assessment within this timeframe, a reminder via email will be sent to the email address provided during the baseline assessment, containing a Qualtrics link to the post-assessment survey. This will allow participants a one-week window to complete the survey, starting from the date of their last uncompleted post-assessment notification.

In Step 4, follow-up data will be collected through a notification will be sent via the TIIM app two weeks after the post-assessment. As with the post-assessment, we will implement the same strategy during the follow-up period, including email reminders, to maximize response rates effectively.

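### The post-follow-up offer to controls carries no eligibility condition, despite a fresh PHQ-9 item 9 answer, and falls after the stated contact support has ended

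*Protocol article*

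**What the plan says.** **The offer.** Section 2.6 (Control group) says: "After the follow-up, participants in the control condition will receive an email offering them the opportunity to randomly receive one of the two interventions". It gives no eligibility or safety condition.

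**The entry rule.** One exclusion criterion in section 2.3 (Study population) is "reporting any suicidal ideation (i.e., scoring above 0 on item 9 of the Patient Health Questionnaire"). The other clinical exclusions there are a severe diagnosis, psychiatric medication, and current treatment for a mental disorder.

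**The reason for it.** Section 2.8 (Procedure) explains the exclusion of ineligible people by the emotional sensitivity of the exercises and "the absence of therapist guidance, which could increase the risk of iatrogenic effects".

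**The action on a positive answer.** Also in section 2.8, anyone giving other than the lowest answer "on item 9 of the PHQ will receive an email containing links to psychological resources for accessing mental health support". It then adds: "These participants will also be excluded from the study". This text stands in the description of Step 1, which opens: "In Step 1, students will begin by completing an initial web-based survey on Qualtrics".

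**Later measurement.** Table 1 schedules the PHQ-9 at screening, post-intervention and two-week follow-up. Section 2.9.1.3 scores all nine items over the last week, so item 9 is included each time.

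**Support.** The limitations paragraph of the Discussion offers contact by phone, text or e-mail for technical problems and for emotional issues caused by the intervention. It dates this from study start to the follow-up assessment.

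**The concern.** The stated reason for the item 9 exclusion concerns receiving the exercises without a therapist. For the two intervention arms the screen comes shortly before the exercises. Controls first receive the exercises after follow-up, so the screen protects them only if the answer has not changed since.

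Followed as written, the plan would e-mail the unguided exercises to a control whose most recent item 9 answer meets the protocol's own exclusion. It would do so after the period in which the article says help is available for emotional reactions. What is at stake is the safety of those controls. The trial's results are not involved.

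**Working it through.** The plan gives no figure to reproduce here. The check compares the rules with one another and does simple arithmetic on the schedule.

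**1. Age of the screening answer at the offer.** Inputs are from section 2.8: a 7-day intervention period, the post-assessment one day later, and follow-up two weeks after that.
- Post-assessment: 7 + 1 = day 8.
- Follow-up: 8 + 14 = day 22.

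Screening precedes app registration and randomization, so it precedes day 1. The screening answer is therefore at least about three weeks old at the earliest possible offer. It is older if the one-week e-mail windows for late assessments are used. Section 2.6 sets no latest date for the offer.

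**2. Is newer information available?** Yes. Table 1 places the PHQ-9 at follow-up, just before the offer, and it refers to the preceding week. The offer does not depend on it.

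**3. The same person at two times, under the rules as stated.**

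| Situation | Item 9 above 0 | Stated consequence for the exercises |
|---|---|---|
| Step 1 survey | Yes | Excluded, resource links sent |
| Control at follow-up | Yes | None stated; section 2.6 sends the offer |

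**4. Exercise period against support period.**

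| Group | When the exercises are done | Inside the stated support period? |
|---|---|---|
| RWM and CWM | Days 1 to 7 | Yes |
| Controls who accept | After follow-up (day 22 or later) | No |

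**5. How many.** Section 2.2 plans 159 participants, allocated 1:1:1, so 159 / 3 = 53 controls are due the offer. The documents give no rate of new answers above 0. For scale only, each 1% of controls newly above 0 would be 53 × 0.01 = 0.53 of a person.

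**The case against.** The strongest reply is that this is silence in a condensed article. A fuller protocol may say what happens to item 9 answers at follow-up, and the entry criteria govern the trial, not a voluntary offer made after the last assessment. That has force, and it limits the point. But the article itself states the offer, the exclusion, the reason for it and the end of support, and these do not fit together for controls.

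A second reply is that the item 9 sentence in section 2.8 names no time point. If it also ran at follow-up, a control above 0 would be excluded and might no longer count among those due the offer. This reading is possible. The text stands in Step 1, between eligibility and the app download, so screening only is the more natural reading. Exclusion from the study would also not clearly govern an offer made once study assessments are over.

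Third, the Discussion does not say that contact is withdrawn from controls who accept, and the same paragraph speaks of contact details being on hand for the whole study. It then fixes the end at follow-up, however, and nothing extends support to the offered module.

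A reader might infer four stronger things that the documents do not support:
- **That people barred at entry later receive the exercises.** They do not, because screening comes before randomization. Only later change matters.
- **That later item 9 answers are ignored in every arm.** The article is merely silent on this, and a full protocol may cover it. For RWM and CWM those answers come after the exercises have ended.
- **That the article calls the offered exercises distressing in section 2.5.1.** That remark concerns the topic of death, which the birthday exercise was adapted to avoid.
- **That the comparison is biased.** The offer comes after the last outcome.

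**Conclusion.** The point holds as a minor, low-cost safety correction. Section 2.6 offers the unguided exercises to all controls without a condition, while the article's own reasoning would withhold them from anyone above 0 on item 9. The current answer is collected at follow-up, and the stated support ends there.

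Up to about 53 controls are due the offer, assuming the planned 159 are enrolled; attrition may lower this. The number who would meet the exclusion by then cannot be derived from the documents and is probably small. The offer can be declined. No outcome, comparison or sample size is affected.

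The conclusion rests on reading the item 9 action as part of Step 1, and on no fuller document holding a condition for the offer. Confidence is medium for that reason.

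**What to change.** In section 2.6:
1. Do not send the offer to controls who score above 0 on item 9 at follow-up. Send it to those who score 0. Those with no follow-up answer may be offered the module subject to step 2.
2. Before the offered module opens, repeat the clinical exclusion questions of section 2.3: item 9, severe diagnosis, psychiatric medication and current treatment. This covers controls without a follow-up answer and the exclusions that are not measured at follow-up. It largely overlaps with step 1 on item 9, so if only one step is adopted it should be this one.
3. Send the section 2.8 resource links to anyone who meets an exclusion in step 1 or 2.
4. Keep the contact support described in the Discussion open while controls use the offered module.

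The cost is a few sentences. The resource e-mail already exists, and addresses are already held, since "a reminder via email will be sent to the email address provided during the baseline assessment". A few controls will not get the offer, those who accept will answer a few extra questions, and the contact line stays open longer. Every step falls after the last outcome, so the analysis is untouched. Section 3 describes the study as ongoing, so the change can apply to offers not yet sent. If all have been sent, the report should say how item 9 at follow-up was handled for them.
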